### Recruitment

The study will be performed in Region Halland, Sweden, as it is a collaborative project between Halmstad University and Region Halland. The organization of the health care system in Sweden is designed so that primary care centers are the main actors and there are district nurses to take care of people with high BP registered in each primary care center. There is an integrated electronic health data system available in Region Halland that facilitates the recruitment process.

First, the primary care centers are strategically chosen, and the responsible heads of the primary care centers receive information regarding the project. Through access to the integrated medical data given the ethical approval, we will select the potential pseudonymized persons with hypertension according to the inclusion criteria described below. Then, staff at Region Halland with authority and access to the integrated medical data will reveal their identities. The contact information will be sent to a district nurse working in this study, who will send invitation letters to each eligible person. The letter will contain information about the purpose, that the research objective is to develop an interactive app for persons with hypertension, methodology for the project, instructions explaining how to join, and the informed consent. It will be clearly stated in the invitation letter that participating in the project is voluntary and does not affect the process of treatment in the primary care center.

A week after, the nurse contacts them by telephone regarding participation in the project. The eligible persons are asked to join the project for the first step of the project (focus groups) and will also be invited to join the second step of the project (pilot intervention) and, if wanted, (only) the third step (longitudinal study). Furthermore, being able to speak and understand Swedish and having their own smartphone will also be inclusion criteria that is checked by the nurse.

#### Inclusion Criteria

The inclusion criteria are as follows: (1) aged 40-70 years; (2) have hypertension diagnosis (ie, International Classification of Diseases, Tenth Revision [ICD-10] codes from I10 to I16 in the person’s medical history) for 1 year or more and have prescribed medications; (3) know Swedish, both spoken and written; and (4) have own smartphone.

#### Exclusion Criteria

In order to alleviate the factors that might affect MA and make it hard to see the effect of the intervention, the following exclusion criteria were applied based on experts’ knowledge: (1) receiving medication with unit-dose packaging (Apodos); (2) previous stroke; (3) myocardial infarction; (4) psychological disorder or cognitive impairment (ie, ICD-10 codes F01 to F99); (5) pregnancy-induced hypertension; (6) insulin treatment; or (7) kidney disease defined as glomerular filtration rate <60 mL/min.

Apodos directly affects MA, especially for the patients with polypharmacy. Psychological disorders or cognitive impairments also affect MA directly due to forgetfulness and other factors related to their disease. We believe this type of patient needs specific types of interventions and should not be included in this study. Patients with psychological disorders (ICD-10 F01-F99) will first be excluded based on their medical health records. Patients with any occurrence of these diagnoses, anywhere in their histories, will be excluded. Additionally, though, there might be some cases of psychological disorders that are not registered in electronic health records as diagnoses. Hence, after the interested participants show up, we will also contact the district nurse at the included primary care centers to detect and exclude if such cases exist in the interested participants. Pregnancy-induced hypertension is partially excluded already, since we included only patients who already have at least 1 year of hypertension. The other exclusion criteria (ie, previous stroke, myocardial infarction, insulin treatment, and kidney disorders) were suggested by clinicians to exclude due to having other complications and treatment plans that might interfere with MA. Excluding all, we have around 12,000 individuals with hypertension in Region Halland who may be interested in participating.

### Data Collection and Analysis

#### Focus Groups

In the focus groups (both the ones conducted for needs assessment and the ones for testing the usability and the translated MUAH-16 questionnaire), approximately 6-8 persons with hypertension per group are included in a total of 4-5 groups. The focus groups last approximately 2 hours. Focus groups are chosen to generate a deeper meaning with varying views through group discussions [38]. Due to the outbreak of COVID-19, the possibility of conducting online or telephone focus groups with 2-4 participants is also considered to avoid any possible infection threat in face-to-face focus groups. In order to measure and describe the participants’ acceptability and usability testing and app usage, a semistructured interview guide will be developed based on a mobile health app usability questionnaire [39] (with 3 subscales: ease of use, interface and satisfaction, usefulness). The data from the focus groups will be analyzed with qualitative content analysis and a manifest approach [40].

#### Longitudinal Study

The data from the participants in the study are sent through their mobile app to the server, where all the participants’ data is stored. All the data from the participants are collected via self-reports and their hypertension-relevant information in the aggregated health database. The only item that we measure without the participants’ engagement is if they have seen the intervention and how long it took to answer the questions. This information is used to measure the user’s fatigue and intervention retention and will be used to adapt the interventions.

The effect of the intervention is analyzed statistically using segmented regression analysis, testing for changes in both the level and the trend of the outcome.

### Intervention Design

The design of the digital intervention module is considered to follow the just in-time adaptive intervention framework (JITAI). JITAI is an intervention design aiming to provide the right type and amount of support at the right time by adapting to an individual's context [41]. It has potential for promoting health behavior change, which in our study is supposed to be MA. The conceptual model of JITAI, including all its components, is shown in Figure 1 (borrowed from Nahum-Shani et al [41]). We explain the details of the intervention design following the JITAI conceptual model.

**Figure 1 figure1:**
[figure not shown]
Conceptual model of just-in-time adaptive intervention components.

#### Intervention Options

Intervention options are a set of possible interventions that are going to be delivered at decision points. In JITAI, intervention options can be various types of support (information, advice, feedback, etc), source of support (mobile, nurse, physician, etc), amounts of support (intensity, dose, etc), and type of media or channel (phone call, SMS text messaging, etc).

From the conducted literature review, we summarized all types of digital interventions delivered to individuals with hypertension as follows: (1) reminders for medication intake (daily or several times per day depending on the antihypertensive medication plan), reminders for BP measurement (every 3 months), and reminders for physical activity (biweekly); (2) informational contents regarding hypertension and all its facts, consequences, treatments, risks, medications and side effects, lifestyle, and so on (text, videos, etc)—the prepared interventions will be based on health care professional advice plus the reference of webpages for further readings; (3) trends on medication intake, physical activity, etc in a feedback motivational message—based on the recent activity of the user, a feedback motivational message is sent biweekly; and (4) motivational messages—the relevant messages are phrased in a motivated manner (eg, regarding smoking, a message like “Treatment of high blood pressure has a much better effect if you do not smoke.”).

#### Distal Outcomes

Distal outcome is the ultimate goal that the intervention is trying to achieve. In iMedA, we considered primary and secondary distal outcomes. Primarily, we aim at improving MA. Then, in the long term, BP is considered as a secondary distal outcome along with increased quality of life [42], assessment of the lifestyle behavior (smoking, alcohol consumption, physical activity, and food intake) [10], and communicative and critical health literacy [43].

In order to measure MA, we consider the following:

Self-reported medication intake through the mobile app is supposed to be collected every day.MUAH-16 [44] is measured before and after the intervention. It is a MA questionnaire for hypertension. It consists of 16 items with four factors: (1) positive attitude towards health care and medication, (2) lack of discipline, (3) aversion toward medication, and (4) active coping with health problems. The items are on a 7-point Likert scale (1=completely disagree to 7=completely agree). A previous study [44] had found correlations between adherence and the MUAH-16 score. Specifically, they found that higher scores in subscale 1 correlated positively with adherence, and higher scores on subscale 2 correlated negatively with adherence.Pickups from pharmacies will be collected after the intervention is finished.

BP is to be measured once before the start of the intervention, at 3 months, and then at 6 months by the recruited nurse.

Health literacy will be measured by the Swedish Communicative and Critical Health Literacy scale. It consists of 5 items with a 5-point Likert scale [43]. Health status will be measured by EQ-5D (EuroQol 5-Dimension questionnaire). It consists of 5 areas for covering health, with 5 response alternatives and 1 overall question regarding health (EQ-VAS [EuroQol visual analogue scale] with score range of 0 to 100) [42]. Both will be measured before and after the intervention.

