**Methods:**

The study design is an interrupted time series. We will collect data on a daily basis, 14 days before, during 6 months of delivering digital interventions through the mobile app, and 14 days after. The effect will be analyzed using segmented regression analysis. The participants will be recruited in Region Halland, Sweden. The design of the digital interventions follows the just-in-time adaptive intervention framework. The primary (distal) outcome is MA, and the secondary outcome is blood pressure. The design of the digital intervention is developed based on a needs assessment process including a systematic review, focus group interviews, and a pilot study, before conducting the longitudinal interrupted time series study.

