## Introduction

### Overview

Hypertension is a common, dangerous, and treatable but undertreated condition worldwide and has a prevalence of approximately 30% in adults [1]. It becomes more common in more advanced ages, and the prevalence increases to 60% in persons over 60 years of age [2]. However, about 33% of persons with hypertension are unaware of their condition [2-4]. The incidence of hypertension in Sweden is estimated at approximately 27% [5]. Although blood pressure (BP) control has increased in Sweden, barely half of the treated patients achieved adequate BP levels [6].

Hypertension causes increased mortality and morbidity, most often by congestive heart failure, ischemic heart disease, and ischemic and hemorrhagic cerebrovascular insults [7]. Hypertension is also associated with increased occurrence of peripheral vascular disease and chronic kidney disease [8,9].

According to the National Board of Health and Welfare in Sweden [10], support and motivation for lifestyle changes as well as for self-care management are the first options when a person is diagnosed with hypertension, that is, having a systolic BP >140 mm Hg and diastolic BP >90 mm Hg measured repeatedly several times (3-6) over weeks or months, after 5 minutes of rest, while sitting with the right arm at heart level [10-12].

Lifestyle changes such as reducing weight, quitting smoking, reducing alcohol, and increasing physical activity are usually supported by visits to the district nurses individually or in groups in order to lower the BP. The support consists of educational and behavioral strategies to motivate and facilitate the person to conduct lifestyle changes in daily life [10]. If the lifestyle changes do not give results in lowering the person’s BP, medication treatment is required.

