#### Longitudinal Study

The longitudinal study is designed to assess the effect of the proposed adaptive digital interventions delivered through the mobile app with individuals with hypertension for 6 months. The design is proposed to be an interrupted time series approach, which is considered to be the strongest quasi-experimental design that can be used to evaluate the effectiveness of an intervention [35,36]. The interrupted time series designs start to collect outcome measures before, during, and after intervention steps. Therefore, they are supposed to capture the level and any trend changes of one or more outcomes through time.

We will keep track of multiple variables for each participant through time and try to deliver the right intervention to the right person through patient-reported measures and app usage.

Two arms are considered in this design: One arm receives digital intervention. We will also add a nonequivalent no-treatment arm. This control group will be picked out of the group of patients who fulfilled the inclusion criteria and for whom the only criteria that are available for comparison is the primary MA (ie, pickups from the pharmacy). The reason to add this control group is to be able to address the internal validity threat [37]. By adding the control group, the effect of history is mitigated, and the study is strengthened against other threats to internal validity such as maturation (does the MA improvement occur naturally over time?).

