## Results

We have started the focus groups, although the COVID-19 outbreak is a big roadblock at the moment. The design of the digital interventions is in progress, and the mobile app will be ready in November 2020. Then, we are planning to run the pilot study. After fixing all the probable modifications due to the pilot evaluations, the longitudinal study will then start in February 2021. We expect to publish the results of the analysis in mid-2021.

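### Blood pressure has one pre-intervention occasion and no control-arm measurement, so drift from repeat visits or season could not be told apart from an app effect

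*Protocol article*

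**What the plan says.** The abstract ranks the outcomes: "The primary (distal) outcome is MA, and the secondary outcome is blood pressure". The Distal Outcomes section fixes the BP schedule: "BP is to be measured once before the start of the intervention, at 3 months, and then at 6 months by the recruited nurse".

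The study is an interrupted time series with data "14 days before, during 6 months of delivering digital interventions through the mobile app, and 14 days after". Those are the daily data; BP is not among them. The Decision Rules section makes the first 14 days after installation a data-collection phase and describes no further BP measurement in it.

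The Longitudinal Study section under Study Design adds a nonequivalent untreated arm to protect against history and maturation, but for that arm "the only criteria that are available for comparison is the primary MA (ie, pickups from the pharmacy"). The Longitudinal Study section under Data Collection and Analysis names segmented regression, testing level and trend, as the effect analysis. It also says that data come from self-report and from "their hypertension-relevant information in the aggregated health database".

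On timing, the Results section says that "the longitudinal study will then start in February 2021".

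**The concern.** An interrupted time series uses the pre-intervention series to show where the outcome was heading. A control series does the same job by showing what happened to similar people over the same dates. For BP the article has neither: one point before, and no BP in the comparison arm.

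Any fall that would have happened anyway over those 6 months therefore lands in the same place as an app effect. There are two obvious candidates. One is a decline as people get used to being measured. The other is a change with season, which for someone starting in February would run from winter into August.

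BP control is part of the stated aim, so a fall in BP is likely to be reported as support for the app. It could appear without any change in adherence. A later analysis plan cannot create pre-intervention measurements that were never taken.

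**Working it through.** **Inputs from the protocol article.** BP at one occasion before the intervention (month 0), then months 3 and 6. Segmented regression for level and trend. No control-arm BP. Planned start February 2021. Intervention group of at least 32 required and 50 planned. Significance level 0.05, sidedness not stated and taken here as two-sided.

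**The plan's own figure.** The 32 comes from a cited simulation for a Poisson series and is not a BP calculation. The article does not give enough to reproduce it, and nothing here depends on it except as a lower value of n.

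**Step 1: can the named model be fitted to BP?**

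The model is y = b0 + b1·t + b2·post + b3·(post × t), with post = 1 after the start.

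| t (months) | intercept | t | post | post × t |
|---|---|---|---|---|
| 0 | 1 | 0 | 0 | 0 |
| 3 | 1 | 3 | 1 | 3 |
| 6 | 1 | 6 | 1 | 6 |

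The t and post × t columns are identical, so the rank is 3 for 4 coefficients. Pre-trend and trend change cannot be separated. More participants on the same schedule add no new time points. By contrast, the daily adherence series (14 + 182 + 14 = 210 days), with two change points, has rank 6 for 6 coefficients. The defect is specific to BP.

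**Step 2: calendar.** February + 14 days + 6 months is mid to late August. For the earliest entrants the three BP occasions therefore fall around February, May and August.

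**Step 3: how often would drift alone give a significant result?** The article specifies no BP test that these data can support, so a two-sided paired t-test at 0.05 stands in for a simple pre-post comparison. With true effect 0 and a non-treatment fall b, the statistic is noncentral t with n − 1 degrees of freedom and noncentrality b·√n / SD. For example, with n = 50, b = 2 and SD = 15, this is 2 × 7.07 / 15 = 0.94. With b = 5 and SD = 10 it is 5 × 7.07 / 10 = 3.54.

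Both b and the SD of change are assumptions; the article gives neither.

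| n | b (mm Hg) | SD 10 | SD 12 | SD 15 |
|---|---|---|---|---|
| 50 | 2 | 28% | 21% | 15% |
| 50 | 3 | 55% | 41% | 28% |
| 50 | 5 | 93% | 82% | 64% |
| 32 | 2 | 20% | 15% | 11% |
| 32 | 3 | 38% | 28% | 20% |
| 32 | 5 | 78% | 63% | 45% |

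With b = 0 every entry is 5%. With a concurrent BP comparator sharing the same drift, the contrast is (effect + b) − b = effect, and the rate under no effect returns to 5%.

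**Step 4: precision.** Assume a visit-to-visit SD of 8 and a within-visit SD of 7 mm Hg.

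- One reading per visit: SD of change = √(2 × (64 + 49)) = 15.0.
- Three readings averaged per visit: √(2 × (64 + 49/3)) = 12.7.
- Three readings per visit and two baseline occasions: √(64/2 + 49/6 + 64 + 49/3) = 11.0.

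Averaging readings narrows the error but removes no seasonal drift. Averaging several baseline occasions can absorb some settling-in.

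**The case against.** A reader might go further than the article allows, in five ways.

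- **A breach of the article's own standard.** The Overview describes BP "measured repeatedly several times (3-6) over weeks or months, after 5 minutes of rest, while sitting with the right arm at heart level". That is the criterion for diagnosing hypertension, and participants have already been diagnosed for at least a year. It shows that the authors know repeated measurement matters. It is not a rule for the outcome, so there is no contradiction.
- **A single cuff reading.** The BP sentence lists occasions. One occasion may include several readings, a detail that an article commonly leaves to the full protocol. If so, the first precision gain in step 4 is already in hand, but the one-occasion problem is unchanged.
- **An unblinded, newly met nurse.** Neither is stated. Lack of blinding is a fair inference, since no masking is described and there is no control-arm BP. Unfamiliarity is not: recruitment involves contact from a district nurse working in the study.
- **A winter-to-summer calendar for everyone.** Only a planned start month is given. The recruitment period is not stated, and later entrants would meet other seasons. The expectation of publishing in mid-2021 does not settle it, because even February entrants would finish after that.
- **Drift that would be read as benefit.** The article does not say how BP will be interpreted and gives no size for any fall. What can be said is that drift could not be told apart from benefit.

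The stakes are also limited: BP is secondary, the hypothesis in the abstract concerns adherence and self-care, and the daily adherence series is unaffected. All of this narrows the point. None of it supplies a BP pre-trend or a BP comparator.

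**Conclusion.** The point holds in a limited form. The article fixes one pre-intervention BP occasion and leaves the comparison group without BP, so its named analysis cannot separate drift from an app effect on the secondary outcome. That rests on the article alone and on the rank argument, with no assumed numbers.

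The size does rest on assumptions. For a non-treatment fall of 2 to 5 mm Hg and an SD of change of 10 to 15 mm Hg, the chance of a significant fall with no true effect is about 15% to 93% with 50 participants, and 11% to 78% with 32. The width of that range shows how little the article allows one to say. The seasonal part applies to those entering near the planned start. The issue deserves correction before enrolment, but it does not touch the primary outcome.

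**What to change.** 1. At each of the three nurse visits, take several seated readings under one written procedure and analyse their mean. If the full protocol already does this, say so.
2. Establish whether the regional health database holds BP values; the article mentions only hypertension-relevant information. If it does, extract them for the year before and for the study period, in both the app and the comparison group. Use them in a supporting analysis as extra pre-intervention points and as a same-calendar comparator. Routine values should be compared with routine values, so that a change of measurement setting does not coincide with before versus after.
3. State that the nurse-measured pre-post BP change is uncontrolled and descriptive, and do not attribute it to the app on its own.

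The cost is a few minutes per visit and a wider extraction. Routine values are less uniform and will be partly missing, and those from 2020 are affected by COVID-19. The two groups are also nonequivalent, so shared drift is itself an assumption. For these reasons the database comparison should support the BP conclusion and not be its sole contrast. If the database holds no usable BP, items 1 and 3 still apply.

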#### Proximal Outcomes

Proximal outcomes are the short-term goals of the interventions. They can be mediators, intermediate measures, or both for the distal outcomes. The medication intake is considered to be the main proximal outcome, which is measured daily. The physical activity rate, which is measured weekly, is another proximal outcome.

Since most of the contents are educational, and they try to increase the hypertension knowledge of the participants, we will add a proximal outcome to measure how much their knowledge has increased. We consider two methods to measure it. First, after showing the content, we will ask “Did you know...?”. Second, we will design simple gamification tests to be presented to the participants biweekly.

To prevent poor adherence to the interventions, it is recommended to define a few proximal outcomes related to intervention engagement and fatigue. Therefore, we consider the number of clicked interventions, dwell time, number of watched videos, and like/dislike feedbacks for each intervention as proximal outcomes related to intervention adherence and retention.

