#### Tailoring Variables

Tailoring variables are information about the participant that is used to decide when to provide which intervention. In other words, they are used to personalize the interventions and make them adaptive to the individual’s circumstances. All proximal outcomes can serve as tailoring variables. They can be measured actively, passively, or both. Active assessments require an individual's engagement in measuring, for example through self-reports, while passive assessments require minimal or no individual engagement, for example through a mobile phone’s sensors.

From baseline information, we can select a few tailoring variables, including alcohol consumption, smoking, specific diet, age, and gender, in order to personalize the interventions. These are considered to be hard-pruning because, with the help of these baseline tailoring variables, a set of intervention options are ruled out from the beginning. As an example, if the person is a nonsmoker, there is no need to motivate him or her to quit smoking.

From the MUAH-16 questionnaire, we start to learn more about an individual’s beliefs, barriers, and behavior about MA. It has 4 subscales regarding (1) positive attitude toward health care and medication, (2) lack of discipline, (3) aversion toward medication, and (4) active coping with health problems. Each subscale contains 4 questions. At the beginning of the intervention, MUAH-16 questions are used as tailoring variables. Then, during the intervention period, and based on the previously delivered informational contents to the individual, the answers to “Did you know...?” questions will be used as tailoring variables.

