#### Decision Rules

Decision rules are the adaptation engine of JITAIs. They are used to determine which intervention option to deliver to whom and when. They are the links between intervention options and tailoring variables. Operationally, a JITAI includes a sequence of decision rules (ie, treatment policies) that take the individual’s current context as input and specify whether an intervention should be delivered now and what intervention should be delivered [45].

Decision rules in iMedA will be probabilistic rules from experts modified by “suggestions” from reinforcement learning [46]. Reinforcement learning is used to continuously learn and optimize the treatment policy in JITAI as the individual experiences the interventions. It automatically “discovers” which interventions are most successful for which patients by using statistical machine learning methods.

Since we are using an interrupted time series design, we will consider the first 14 days after the app installation to be the preintervention phase (ie, data collection). Figure 2 shows the flowchart of these initial 14 days in more detail.

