**Figure 2 figure2:**
[figure not shown]
An illustration of the preintervention step (ie, the first 14 days). HL: health literacy; MUAH-16: 16-item Maastricht Utrecht Adherence in Hypertension; QoL: quality of life.

At the beginning of the intervention delivery, the JITAIs will be delivered based on expert suggestions, taking into account the answers to the initial questionnaires, to provide baseline data that a reinforcement learning agent can use to improve upon without the necessity for a warm-up period characterized by random interventions. To allow the agent to learn effectively from collected data, the expert decision rules will be defined in a probabilistic manner, allowing off-policy evaluation. The agent will be built upon a contextual bandit framework that uses tailoring variables to adaptively suggest interventions to improve proximal outcomes and, ultimately, distal outcomes. The agent will optimize the decision rules on a biweekly basis, allowing evaluation before deployment, as illustrated in Figure 3.

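### Knowledge gain is named as a proximal outcome, but its first measure is a self-report taken after the content and no knowledge test is described before content starts

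*Protocol article*

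**What the plan says.** The Proximal Outcomes section states the aim as a change: "we will add a proximal outcome to measure how much their knowledge has increased". It gives two methods. The first fixes an order: "after showing the content, we will ask" the did-you-know question. The other is a repeated quiz: "Second, we will design simple gamification tests to be presented to the participants biweekly". The text does not say when the first quiz falls, what it covers, or whether items recur.

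The Tailoring Variables section gives the first method a further use. During the intervention, answers to these "questions will be used as tailoring variables", and they are tied there to content the person has already received.

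On timing, the Decision Rules section says "we will consider the first 14 days after the app installation to be the preintervention phase". The abbreviation legend of Figure 2, which illustrates those days, reads "HL: health literacy; MUAH-16: 16-item Maastricht Utrecht Adherence in Hypertension; QoL: quality of life". For health literacy and health status, the Distal Outcomes section states "Both will be measured before and after the intervention", and it gives MUAH-16 the same schedule. It contains no such statement for hypertension knowledge.

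**The concern.** An increase is a difference between two values, one of them taken before exposure. The first method takes its only value after exposure: the participant has just been told a fact and is asked whether it was already known. Some who did not know it will say that they did, because the fact now seems familiar or because admitting ignorance is uncomfortable. The second method may be a real test, but nothing in the text places one before content delivery begins.

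Two things are at stake. A reported knowledge gain might rest on recalled self-judgement, or on change counted from some point after the content had started. In addition, the did-you-know answers are tailoring variables, and the Contextual Bandit Formulation section treats tailoring variables as the context from which content is chosen. A systematic false yes therefore also reaches the selection of content.

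**Working it through.** The plan states no figure for knowledge, so there is none to reproduce. The check compares what each method observes with what the outcome requires.

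**What is required.** Let K0 be knowledge before the first content and K1, ..., Kn the scores at later tests. Gain from baseline is Kn − K0.

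**Method 2, the repeated quiz.** Kn − K0 = (Kn − K1) + (K1 − K0). If items are comparable, the quizzes observe the first bracket. They observe the second only if a test precedes the first content. The text describes no such test.

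**How loose a post-exposure score alone is.** With a proportion correct p after exposure and an unknown prior proportion between 0 and 1, the gain lies between p − 1 and p. With an assumed p = 0.80, the range is 0.80 − 1 = −0.20 to 0.80, that is, −20 to +80 percentage points.

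**Method 1, did-you-know after the content.** This is narrower than the bound above, because a no answer carries information about prior knowledge. Let u be the share who truly did not know an item and h the share of those who say afterwards that they did. Ignoring errors in the other direction, the observed share of no answers is u × (1 − h). Neither u nor h is in the document; both are assumed here.

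| u | h | observed u(1 − h) | shortfall u × h |
|---|---|---|---|
| 0.50 | 0.10 | 0.45 | 0.05 |
| 0.50 | 0.25 | 0.375 | 0.125 |
| 0.50 | 0.50 | 0.25 | 0.25 |

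The item thus gives an estimate of novelty that is biased by an unknown amount. It says nothing on whether the fact was retained.

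**Can another comparison replace the baseline?** No. In the Longitudinal Study part of Study Design, the control group is available for comparison on pharmacy pickups only. It supplies no knowledge data.

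**Was a baseline test perhaps planned elsewhere?** MUAH-16, health literacy and health status have an explicit before-and-after schedule in the text; knowledge has none. The Figure 2 legend lists no knowledge test, but a legend that expands abbreviations is not a full list of assessments, and the figure itself was not available. The absence is therefore one of description in the text.

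**The case against.** The strongest case on the other side has five parts.

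- **The outcome can still be estimated to some degree.** A reader might infer that knowledge gain cannot be measured at all. The document does not support that. A no to the did-you-know item is a retrospective pre-test, biased but informative, and repeated quizzes with comparable items would show change within the intervention. This stands.
- **Some tempting details are not stated.** A reader might infer that the question appears with the answer still on screen, that the quizzes cover only content already delivered, or that all gain in the first fortnight is lost. The text gives no screen layout, quiz content or first quiz date. None of these readings is relied on here.
- **A condensed article may omit a baseline test.** Figure 2 could show one, and the tests were still to be designed. This stands as a limit on the second half of the point. It does not touch the first half, because the order of the did-you-know question is stated outright.
- **The obvious repair has faults.** Moving a question of the form 'did you know that X' ahead of its content still discloses X. A quiz early in the pre-phase could also act as a cue within the only baseline segment of the daily intake series. Both objections are sound, and they determine the form and the place of the fix.
- **The consequence is small.** Medication intake is the main proximal outcome. Knowledge is neither the primary nor a listed distal outcome and plays no part in the sample-size argument. This stands.

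**Conclusion.** The point holds in a limited form. The article names an increase in knowledge as an outcome. Its first method is a post-exposure self-report, and the text describes no knowledge test before content delivery. Increase from baseline is therefore not directly measured unless a comparable test is given before the first content.

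The size of the bias cannot be derived from the document. Under the assumed 50% of participants new to an item, the shortfall is 5 to 25 percentage points for hindsight shares of 10% to 50%. These inputs are illustrative only.

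A reader might also infer that the adaptive engine is materially misled. The text shows only that these answers enter as context. It does not say which responses form the reward, and the effect on content selection cannot be derived. The primary outcome and the sample size are unaffected, so this is a desirable improvement and not a serious flaw.

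**What to change.** - Give one short knowledge test at the end of the 14-day pre-phase, after the last baseline intake report and before the first content. The baseline intake series is then complete before any cue from the test can act.
- Repeat the same items in the last fortnight of the intervention, and define knowledge gain as the within-person difference between the two.
- Use the did-you-know answers as a self-report of novelty for tailoring, not as the measure of gain. If prior knowledge of an item is wanted, replace the question with one that does not disclose the answer, asked before the content.
- If Figure 2 or the full protocol already contains a knowledge test before content starts, say so in the Proximal Outcomes section and confirm that its items recur at the end.

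The cost is a few minutes per participant and a slight testing effect. The Results section describes the digital interventions as still in design, so the change could be made before the longitudinal study.
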